## Abstract

Loneliness is a significant problem for young people and is associated with a range of physical and mental health difficulties. Meta-analyses have identified that interventions aimed at young people who report loneliness as their primary problem are lacking within the literature. In adults, the most effective interventions for loneliness are those which target the underlying maladaptive social cognitions. Therefore, we have developed a modular Cognitive Behavioural Therapy (CBT) intervention for children and young people. The aim of this study is to conduct a multiple baseline single-case experimental design (SCED) to assess the efficacy, feasibility and acceptability of this intervention. In total 6–8 11–18-year-olds and their families will be recruited. The design consists of AB+ post-intervention, where A is the baseline phase, B is the intervention phase and then a post-intervention phase. Participants will complete a baseline assessment, before being randomised to one of four different baseline lengths (12 days, 19 days, 26 days or 33 days). Participants will then complete an average of 12 sessions of CBT, with the aim being to reduce their feelings of loneliness. Participants will then complete a 12-day post-intervention phase. Participant loneliness will be repeatedly assessed throughout the three phases of the intervention using the Three-item Loneliness Scale, which will be the primary outcome. Secondary outcomes will be reliable and clinically meaningful change on the UCLA Loneliness Scale, Revised Child Anxiety and Depression Scale (RCADS) and Strengths and Difficulties Questionnaire (SDQ). Feasibility and participant satisfaction will also be assessed and reported.

**Trial registration: ClinicalTrails.gov trial registration number:**
NCT05149963 (Date registered: 07.12.2021). https://www.clinicaltrials.gov/ct2/show/NCT05149963?term=cbt&cond=loneliness&draw=2&rank=1.

## Introduction

Loneliness is defined as the discrepancy between actual and desired social interaction [1]. Temporary loneliness is a normal phenomenon and regarded as part of everyday life [1, 2]. Research suggests that spending time alone is a normative adolescent experience and part of the developmental task of becoming independent, with some young people reporting time alone to be important for the development of self-identity [3]. This is differentiated from chronic loneliness, where an individual experiences a lack of satisfying relationships over time [4].

Chronic loneliness is a transdiagnostic problem and associated with a range of physical and mental health difficulties [5, 6]. Loneliness also increases the likelihood of mortality by 26% even when controlling for multiple covariates [7]. Loneliness in children and young people is associated with higher levels of peer victimisation [8, 9], lower self-worth and a range of mental and physical health problems [10–14]. The population of young people who are at an elevated risk of loneliness is highly heterogenous. It includes those with chronic health problems [15], mental health difficulties [10, 11] and those on the autism spectrum [16]. It is also hypothesised that interventions aimed at reducing loneliness may be an important active ingredient in the prevention and treatment of anxiety and depression in young people [17].

Distinct developmental trajectories of youth loneliness have been identified. It has been found that 18% of young people present with moderate levels of loneliness which increase over time and 22% present with consistently high levels of loneliness throughout childhood [14]. These findings are of significant concern, as it suggests that for many young people loneliness does not spontaneously remiss without intervention. Loneliness in young people is a significant challenge cross-culturally [18], including within the United Kingdom where 10% of children are reported to often experience loneliness, with 14% of those aged 10–12 and 8.6% of those aged 13–15 reporting that they “often” feel lonely [19].

Psychological interventions can be effective in reducing loneliness across the lifespan [20]. A recent meta-analysis of interventions for loneliness in young people highlighted a range of approaches that may reduce loneliness as a secondary outcome in at-risk groups [21]. These included intrapersonal strategies (e.g., psychological therapy), interpersonal strategies (e.g., social skills interventions), social strategies (e.g., social support) and self-help strategies (e.g., therapeutic apps). However, interventions specifically aimed at young people who report loneliness as their primary difficulty (rather than those at-risk of loneliness) are lacking within the literature. The authors also highlighted that current interventions do not differentiate between transient and chronic loneliness; with the latter requiring interventions targeting the underlying anxieties and negative cognitive biases that maintain chronic loneliness. A further limitation of the current evidence base is the lack of controlled experimental designs, which limits the conclusions that can be drawn regarding the efficacy of reported interventions.

A meta-analytic review of adult loneliness interventions by Masi et al. [22] identified that the most efficacious interventions were those which targeted the underlying maladaptive social cognitions. This may also be the case for youth populations and indicates that interventions aimed specifically at reducing loneliness in children and young people should be based within a Cognitive Behavioural Therapy (CBT) framework. However, this finding was not replicated in a recent systematic review and meta-analysis by Hickin et al. [20], which found CBT to be the third most effective treatment approach behind a reminiscence intervention for older adults and social identity interventions. This suggests that interventions for loneliness should take a modular approach, incorporating different evidence-based treatment components which can be selected based upon treatment need. A modular approach may be particularly appropriate for the adolescent population, due to the high levels of heterogeneity in the presentations of young people presenting with chronic loneliness [10, 11, 15, 16].

Käll et al. [23] have developed a modular cognitive behavioural analysis of chronic loneliness based upon a common elements approach. They identified the common practice elements within existing interventions shown to reduce loneliness and identified the ‘target’ mechanisms for a modular loneliness intervention. The modular model has varying treatment implications and its modular nature means it can be applied flexibly to different populations. A modular approach may be particularly appropriate for this client group, as the population is highly heterogenous and it is not yet known what interventions work for whom [17]. Interventions informed by this modular formulation have since been shown to be efficacious in two online randomised controlled trials (RCT) for reducing loneliness in adulthood [24, 25]. This suggests that this formulation model provides a good underlying theoretical basis for the development of Cognitive Behavioural Therapy (CBT) for loneliness in children and young people.

Associations between parental and child mental health problems have been identified, with parental mental health problems predictive of poorer CBT outcomes in young people [26, 27]. Therefore, in this present study parental health will also examined, to assess whether there is preliminary evidence for it having a role in treatment response.

The modular CBT intervention developed for this study will be evaluated through a multiple baseline single-case experimental design (SCED) [28–30]. A criticism of previous loneliness interventions for children and young people has been the lack of controlled experimental designs [21]. SCED’s provide a controlled experimental approach from which causal inferences can be drawn and give the detail and richness commonly associated with case studies [28]. As this is the first study to test this intervention, an iterative approach will be taken to development based upon Plan-Do-Study-Act (PDSA) cycles [31]. PDSA cycles are an individualised quality improvement method which aims to maximise the feasibility and acceptability of interventions by providing a framework for development, testing and implementation of change [32]. This approach has also been used effectively in previous intervention development studies for children and young people [33].

### Aims and objectives

The primary objective will be to evaluate the efficacy of CBT for loneliness in children and young people ages 11–18. The primary outcome will be differences in scores on the Three-Item Loneliness Scale [34] between baseline and intervention and baseline and post-intervention. It is hypothesised that there will be a significant decrease in self-reported loneliness across both time-points. The secondary outcomes will be self-reported loneliness scores on the UCLA Loneliness Scale (UCLA-LS-3) [35] and self and parent-reported scores on the Strengths and Difficulties Questionnaires (SDQ) [36] and Revised Child Anxiety and Depression Scale (RCADS) [37]. It is hypothesised that there will be a reliable and clinically meaningful change [38] in total loneliness scores on the UCLA-LS-3, in the impact scores on the SDQ and in total anxiety and depression scores on the RCADS.

The secondary objective is to evaluate the feasibly and acceptability of the intervention process. This will be defined in terms of a) meeting the recruitment target, b) participant retention and c) participant feedback of the intervention using the Experience of Service Questionnaire [39].

## Methods

### Study design

The efficacy of CBT for loneliness in children and young people will be evaluated through a randomised multiple-baseline single-case experimental design (SCED) [28–30]. The design consists of AB+ post-intervention, where A is the baseline phase, B is the intervention phase and then a post-intervention phase. In the SCED approach participants are repeatedly assessed on at least one independent variable, in this case self-reported loneliness on the Three-item Loneliness Scale [34], across each phase of the intervention. This repeated measurement and within subject replication is then used to test the effects of the intervention for individual participants [28, 30]. Multiple-baseline SCEDs are a controlled experimental approach, with multiple-baselines protecting against threats to internal validity [40].

The construction of this SCED trial and the reporting of the results will be in accordance with the Single-Case Reporting Guidelines in Behavioural Intervention (SCRIBE) [30].

The study has received ethical approval from Royal Holloway, University of London on 22.03.2021 (ethical approval number: 2489). The study was registered with ClinicalTrials.gov on 07.12.2021 (registration number: NCT05149963).

### Procedure

The trial procedure is shown in the schedule of enrolment, interventions and assessments (Fig 1).

**Fig 1 pone.0278746.g001:**
[figure not shown]
Showing the trials schedule of enrolment, interventions and assessments.

Participants will be recruited via advertisements emailed to schools, shared via social media and word of mouth. Participants and their parents/carers will be sent an electronic information sheet and given the opportunity to ask any questions before completing an online consent form. Participants will provide informed ascent as they are under 18, with parents/carers providing informed consent. Participants and their parents/carers will then complete a baseline eligibility assessment. They will complete a range of online questionnaires via Qualtrics [41], a secure online platform. They will then attend a remote research assessment appointment to determine whether the family meet the eligibility criteria. The researcher completing the baseline and post-intervention assessments will not be involved in the clinical intervention and will be blinded to baseline allocation. After all baseline assessments for the participant group are completed, they will be discussed within supervision to confirm that the participants meet eligibility criteria. Eligible participants will then be randomised using a random number generator to one of four different baseline lengths (12 days, 19 days, 26 days or 33 days [42]. The decision to have a minimum of 12 observations per phase meets the requirements for guidelines and standards [43] and will allow for sufficient power for Tau-U analysis [44, 45].

Each of the families will then be contacted to inform them of their allocation. Randomisation and contacting of the families will be completed by a third researcher, who is not involved in either the clinical intervention or research assessments. Families will receive a £25 voucher for completing the baseline eligibility assessment. A letter will also be sent to their General Practitioner (GP) informing them of the family’s participation in the research study. The setting for the entire study will be remote via Zoom [46], with participants recruited from across the United Kingdom (UK).

All participants in the group will begin their baseline phase concurrently. During the baseline phase participants will be asked to complete the Three-Item Loneliness Scale [34] each day via Qualtrics [41]. SMS message reminders will also be sent to the young people and their parent/carers each day.

The baseline phase will be immediately followed by the intervention. Each family will receive (on average) 12 sessions of CBT for loneliness in children and young people. Where possible the first 4 sessions will take place bi-weekly, the second 4 sessions weekly and the final 4 sessions fortnightly.

For all participants the first two sessions will be focussed on assessment and then formulation. The final session for all participants will focus on relapse prevention. During the assessment session the participant will be asked to define 3 goal-based outcomes (GBOs) [47] for how they hope the intervention will reduce their loneliness, which will then guide the treatment process. During the intervention phase the participants will complete routine outcome measures (ROMs) for each session. This will include the Three-Item Loneliness Scale [34], visual analogue scales (VAS) of mood, anxiety and loneliness and ratings of their goal-based outcomes [48]. The ROMs will be completed via Qualtrics [41] before each session. If participants have not completed the ROMs before their appointment, then they will be completed with the clinician at the start of the session.

Participants will begin the post-intervention phase immediately after the final session of their intervention. During the post-intervention phase participants will be asked to complete the primary outcome measure, Three-Item Loneliness Scale [34], each day for 12 days. They will then complete their post-intervention assessment with the second researcher. Before the assessment they will be asked to re-complete the baseline questionnaires in addition to the parent and child-report versions of the Experience of Service Questionnaire [39] and a questionnaire asking whether COVID-19 or any other events have affected them during the intervention period. The family will be given a £25 voucher for completing the post-intervention assessment. A letter will be sent to their General Practitioner (GP) informing them of their participation in the research study has finished.

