### Participants

We will aim to recruit 6–8 participants to the study. All participants will be recruited from within the United Kingdom. Participants must meet the following inclusion/exclusion criteria:

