#### Feasibility and satisfaction measures

The proportion of our minimum recruitment target of 6 participants that we achieve will be reported. Successful completion of 6 participants will indicate that the recruitment protocol is feasible. The proportion of participants retained, defined as completing both the baseline and intervention assessments will be reported; with an 80% retention rate indicating that the research protocol is feasible, based on previous studies [71]. We will also report the proportion of appointments attended across all participants. The key themes identified in the Experience of Services Questionnaire [39] and the questionnaire assessing the impact of COVID-19 or other events on the child’s loneliness will also be reported. Acceptability will be indicated by 80% positive responses on the Experience of Services Questionnaire [39].

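### Allocating 6–8 participants to four baseline lengths by random number generator, with no stated restriction, can leave lengths empty and weaken the stagger; a shuffled balanced list prevents this at almost no cost

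*Protocol article*

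**What the plan says.** All references are to the protocol article.

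- **Allocation (Procedure).** "Eligible participants will then be randomised using a random number generator to one of four different baseline lengths", namely "12 days, 19 days, 26 days or 33 days". No blocking, quota, minimum per length or rule that every length must be used is stated. The sentence cites an outside source that is not available here.
- **Timing (Procedure).** Eligibility is settled for the group before anyone is randomised: "After all baseline assessments for the participant group are completed, they will be discussed within supervision". A third researcher, independent of therapy and assessment, then randomises and informs the families.
- **Start (Procedure).** "All participants in the group will begin their baseline phase concurrently".
- **Sample size (Participants).** "We will aim to recruit 6–8 participants to the study". The section on feasibility and satisfaction measures treats 6 as the minimum target.
- **Role of the baselines (Study design).** "Multiple-baseline SCEDs are a controlled experimental approach, with multiple-baselines protecting against threats to internal validity".
- **Analysis (Data analysis).** Visual inspection, and Tau-U for each case with a weighted average across cases. No randomisation test is planned.

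**The concern.** There is no parallel control group. The main way to tell a treatment effect from something that happened to everyone at once is that treatment starts on different dates for different participants. Because baseline begins concurrently within a group, those dates differ only through the allocated baseline lengths.

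Six to eight people drawn independently into four cells often miss a cell, and sometimes pile up in one or two. Fewer distinct start dates, or several people sharing a date, make it easier for an outside event near that date to look like a treatment effect in several participants. The authors recognise such events as a threat, since they collect reports on COVID-19 and other events at the post-intervention assessment.

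**Working it through.** The article gives no figure for how participants spread over the lengths, so there is nothing to reproduce.

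**Inputs**
- Number of lengths: 4 (Procedure).
- Number of participants n: 6, 7 or 8 (Participants).
- Assumption, not stated in the article: each participant is drawn independently, with probability 1/4 for each length.

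**Formulas.** Of the 4^n equally likely allocations:
- all four lengths used: 4^n − 4·3^n + 6·2^n − 4
- exactly three used: 4·(3^n − 3·2^n + 3)
- exactly two used: 6·(2^n − 2)
- one used: 4

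For n = 6: 4096 − 2916 + 384 − 4 = 1560; 4·(729 − 192 + 3) = 2160; 6·62 = 372; and 4. These sum to 4096.

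| Lengths used | n = 6 | n = 7 | n = 8 |
|---|---|---|---|
| all four | 1560/4096 = 38.1% | 8400/16384 = 51.3% | 40824/65536 = 62.3% |
| exactly three | 2160/4096 = 52.7% | 7224/16384 = 44.1% | 23184/65536 = 35.4% |
| exactly two | 372/4096 = 9.1% | 756/16384 = 4.6% | 1524/65536 = 2.3% |
| one | 4/4096 = 0.10% | 4/16384 = 0.02% | 4/65536 = 0.006% |
| **at least one empty** | **61.9%** | **48.7%** | **37.7%** |
| **two or fewer used** | **376/4096 = 9.2%** | **760/16384 = 4.6%** | **1528/65536 = 2.3%** |

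Full enumeration of all allocations gives the same results.

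**Crowding.** With 6 participants, four or more share one length in 616/4096 = 15.0% of allocations. With 8, the even split of two per length arises in only 8!/(2!)^4 = 2520 of 65536, or 3.8%.

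**What is left of the stagger.** The lengths are 7 days apart. If two lengths are used, treatment starts differ by 7 days at the least (adjacent lengths) and 33 − 12 = 21 days at the most. If three are used, the starts span 14 or 21 days.

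**Smaller groups.** If participants were randomised in separate groups, loss of lengths within a group would be more likely. For a group of 4, at least one length is empty with probability 90.6%, and two or fewer are used with probability 34.4%.

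**After the fix.** With a permuted list of 2,2,1,1 (n = 6), 2,2,2,1 (n = 7) or 2,2,2,2 (n = 8), the probability of an empty length at randomisation is 0. If one participant is then lost at random, the chance of dropping to three lengths is 2/6, 1/7 and 0, and a drop to two is impossible. For comparison, under simple randomisation with 5 of 6 retained, at least one length is empty with probability 76.6%.

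**The case against.** The strongest objection is that the premise comes from silence. A random number generator is also what one would use to shuffle a balanced list. The article is a condensed account, and a restriction could sit in a fuller document or in the cited source. This stands as a condition on the percentages: the article does not call the scheme unrestricted, and a reader should not take that as stated. It does not remove the point. The article does describe how each participant reaches a length, its plain reading is simple randomisation, and a better method is available.

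The second objection concerns the harm. A reader might infer that the staggered starts are the trial's only control, or that clustering on one or two lengths makes effects inseparable from calendar events. The article supports neither.
- Study design also relies on repeated measurement and within-subject replication. Data analysis examines the baseline for stability and lets Tau-U adjust for baseline trend. Families are asked about outside events. The stagger is the main protection against concurrent events, not the only safeguard.
- Two lengths still separate the starts by 7 to 21 days. True inseparability needs everyone on one length, with probability 0.1% or less.
- The common shortfall is three lengths, which still gives staggered starts. Tau-U is computed case by case and does not require all four lengths to be filled.

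Third, a balanced list does not replicate every length: two lengths have a single participant at n = 6, and one does at n = 7. That is true, and it follows from the sample size. The list still ensures that each length is used.

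**Conclusion.** The point holds in a limited form. On the plain reading of the Procedure section, the allocation leaves at least one of the four baseline lengths empty with probability 62%, 49% or 38% for 6, 7 or 8 participants, and leaves two or fewer in use with probability 9.2%, 4.6% or 2.3%. At the minimum target of 6, the trial would more often than not lack one of its four start points. The consequence is a weaker safeguard against concurrent events; its outright loss is very unlikely.

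The figures assume equal and independent draws and a single group of 6–8. They do not apply if a restriction exists elsewhere, and they understate the loss within a group if several smaller groups are randomised separately. The change is worth making because the risk is avoidable and the procedure already contains everything needed to avoid it.

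**What to change.** State in the Procedure section that, once a group is confirmed eligible, the third researcher randomly permutes a balanced list of baseline lengths and assigns it to the participants:
- 8 participants: 2,2,2,2
- 7 participants: 2,2,2,1
- 6 participants: 2,2,1,1

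For 6 and 7, the lengths that appear twice are themselves chosen at random. If participants are randomised in more than one group, balance the list within each group as far as its size allows. If allocation is already restricted in this way, one sentence saying so is enough.

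The cost is about one line of procedure. Eligibility is settled for the group first, so the number to allocate is known, and an independent researcher already does the randomisation. Because the group is allocated after eligibility is decided, the restricted list gives nobody a chance to steer enrolment. The lengths, measures, sessions and planned analysis are unchanged. The case for the change does not depend on a randomisation test, since the protocol plans only visual analysis and Tau-U.

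### Twelve observations per phase is an expected count, not a minimum, in the intervention phase, and the first reading counted there precedes all treatment

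*Protocol article*

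**What the plan says.** All of the scheduling text is in the Procedure section of the protocol article.

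- **Stated property.** "The decision to have a minimum of 12 observations per phase meets the requirements for guidelines and standards [43". The same sentence adds that this "will allow for sufficient power for Tau-U analysis [44, 45". No power, significance level or effect size is given.
- **Baseline.** Participants are randomised to "one of four different baseline lengths (12 days, 19 days, 26 days or 33 days". "During the baseline phase participants will be asked to complete the Three-Item Loneliness Scale [34] each day via Qualtrics [41", with daily SMS reminders to the young person and the parent or carer.
- **Intervention.** "Each family will receive (on average) 12 sessions of CBT for loneliness in children and young people". No lower limit is stated. The primary scale is one of the routine outcome measures (ROMs), collected once per session with goal ratings and visual analogue scales. On timing and mode, the article says: "The ROMs will be completed via Qualtrics [41] before each session". It then sets a fallback for forms that are still outstanding when the appointment begins: "If participants have not completed the ROMs before their appointment, then they will be completed with the clinician at the start of the session".
- **Early sessions.** "For all participants the first two sessions will be focussed on assessment and then formulation".
- **Post-intervention.** The primary scale is completed daily for 12 days.

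Aims and objectives and Data analysis (Primary outcome measure) name two primary comparisons by Tau-U: baseline versus intervention, and baseline versus post-intervention.

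**The concern.** The article claims a property for every phase that its own schedule secures for only two of them. Guideline compliance and power both rest on that property.

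Two further features affect the same primary comparison. First, a reading taken before session 1 is counted as an intervention reading although nothing has yet been delivered, which pulls Tau toward zero. Second, the frequency and setting of reporting change at the moment treatment starts. Study design relies on multiple baselines to protect internal validity. Staggered starts guard against events shared in calendar time, but a measurement change at each participant's own phase boundary moves with the stagger. Replication across cases would replicate any artefact, and the weighted average across cases would carry it forward.

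**Working it through.** **1. Reproducing the figure of 12.**

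| Phase | Rule in Procedure | Scheduled readings |
|---|---|---|
| Baseline | daily, 12 to 33 days | 12, 19, 26 or 33: minimum 12 reproduced |
| Intervention | one per session, 12 sessions on average | mean 12, no floor: minimum not reproduced |
| Post-intervention | daily, 12 days | exactly 12: reproduced as a scheduled count |

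**2. How often the intervention phase would fall short.** The article gives no spread for the number of sessions. Assume a between-participant SD of 1, 2 or 3 and a normal approximation with continuity correction.

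- P(fewer than 12) = Φ((11.5 − 12)/SD) = 0.31, 0.40 or 0.43.
- P(at least one of 6 participants) = 1 − (1 − P)^6 = 0.89, 0.95 or 0.97.

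**3. Dilution of Tau.** The basic A-versus-B Tau averages over all baseline-intervention pairs. A reading taken before any effect contributes zero in expectation, so under an abrupt effect the expected Tau is multiplied by (readings after onset)/(all intervention readings).

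- Effect from session 1 onward: 11/12 = 0.92.
- No effect until after the assessment and formulation sessions (an added assumption): 9/12 = 0.75.

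A simulation of Tau without baseline-trend correction agrees. It used 12 baseline and 12 intervention readings, independent normal scores and an assumed 1 SD shift. Mean Tau was 0.518 with no pre-effect reading, 0.479 with one (ratio 0.92) and 0.390 with three (ratio 0.75).

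**4. Illustrative power per participant.** Same simulation, two-sided 0.05, 4,000 runs, 12 baseline readings. The shift sizes and the 8-session case are assumptions.

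| Intervention readings | Shift 1 SD | Shift 1.5 SD |
|---|---|---|
| 12, all after onset | 63% | 93% |
| 12, one before onset | 55% | 87% |
| 12, three before onset | 38% | 67% |
| 8, one before onset | 40% | 71% |

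**5. Change of schedule at the phase boundary.** Procedure spaces the 12 sessions in three blocks of four: bi-weekly, weekly, fortnightly. From first to last reading this is about 12 weeks if bi-weekly means twice a week, or 18 weeks if it means every two weeks. That gives 12/85 = 0.14 or 12/127 = 0.09 readings per day, against 1 per day at baseline.

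To see what a reporting shift could do, assume one of 0.3 to 0.5 SD with no treatment effect. A significant Tau then appears in about 11% to 21% of cases with 12 baseline readings and 13% to 29% with 33, against a nominal 5%. The article gives no information on whether such a shift exists or which way it would run.

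**6. Slack in the 12-day phases.** If 95% or 90% of daily readings are completed (assumed), all 12 are obtained with probability 0.95^12 = 0.54 or 0.90^12 = 0.28.

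**The case against.** The strongest reply is that only one sentence is demonstrably wrong. Several stronger readings are tempting, and the article does not support them.

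- **That 12 readings are not delivered.** A participant with 12 or more sessions and complete forms has 12 readings. The text supports not guaranteed, no more.
- **That power is inadequate.** No effect size, significance level or target is given, and the cited sources are not available here. The power statement is unsupported for this phase; it is not shown to be false.
- **That reporting switches from private forms to forms filled in with the therapist.** Qualtrics is the default in both phases, and completion with the clinician is a fallback of unknown frequency. The article does not describe baseline reports as private; parents and carers also receive the reminders.
- **That three of 12 readings are untreated and cap Tau at 0.75.** The Intervention section and Table 1 make assessment and formulation Modules 1 and 2 of the treatment, and Module 2 includes psychoeducation. Only the first reading precedes treatment. The 0.75 is an expected multiplier under an extra assumption, and an observed Tau can exceed it.

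Less frequent measurement over a treatment phase of several months is also a defensible way to limit burden on 11- to 18-year-olds. Three of the four baseline lengths have room for missed days, and losing one reading of 12 changes Tau little. The Limitations section already urges caution.

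All of this limits the size of the point. What remains is the conflict over the minimum, the pre-treatment reading counted as intervention, and the schedule change aligned with phase.

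**Conclusion.** The point holds in limited form and should be fixed; it does not threaten the study as a whole. The minimum of 12 is a mean in the intervention phase, and the power claim has no stated basis there. On the documents alone, the dilution of the expected baseline-versus-intervention Tau is a factor of about 0.92 at 12 sessions, assuming an abrupt effect and complete readings. It reaches 0.75 only if nothing happens until after the formulation session.

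The change from daily to session-tied reporting, with a clinician-assisted fallback, is a risk of artefact. A reader might infer that the comparison is confounded in a known direction, but the article gives neither size nor direction. Baseline versus post-intervention is daily in both phases and is free of the dilution and the schedule change. Its only weakness here is that 12 scheduled days leave no room for a missed one.

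The power and false-positive figures rest on assumed shifts and ignore autocorrelation and baseline-trend correction. They show scale only.

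**What to change.** 1. **Reconcile the Procedure text.** Limit the minimum of 12 and the power statement to scheduled baseline and post-intervention readings. Give the intervention-phase count as an expected number, and say that one fewer follows the start of treatment. The number of sessions is a clinical matter and need not change.
2. **Assign the reading before session 1 to baseline** in the Tau-U analysis, and fix this rule before data are seen. That reading is session-tied and may be clinician-completed, so step 3 applies to it too.
3. **Record which readings were completed with the clinician**, and repeat the primary analysis without them.
4. **State that baseline versus post-intervention is the comparison with matched daily measurement**, and that baseline versus intervention is read with that caution.

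These four steps cost a few sentences, one data field and one repeat analysis.

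Optional, at modest participant burden: collect extra Qualtrics readings on fixed non-session days throughout the intervention phase, with the same prompts as baseline, and add a few days to the post-intervention phase to allow for missed days. Daily readings confined to the first three weeks would help less. If bi-weekly means twice a week, session 3 falls at about day 7, so about 7/21 = 33% of those readings would still precede it, and a second schedule change would be added within the phase. The optional step has to be settled before data collection, because readings not taken during treatment cannot be recovered.
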